**Study Summary**

| **TITLE** | Glycaemic Variability in Acute Stroke |
| --- | --- |
| **DESIGN** | Observational cohort study |
| **AIMS** | Establish the impact of glycaemic variability on outcomes in acute stroke |
| **OUTCOME MEASURES** | **Glycaemic Primary outcome:** Mean absolute glucose (MAG) change during initial 72 hours after confirmed stroke  **Stroke Primary outcomes:** National Institutes of Health Stroke Scale (NIHSS) and Modified Rankin Scale (MRS) |
| **POPULATION** | N=200 with or without diabetes in 1:1 ratio |
| **ELIGIBILITY** | Acute Stoke (NIHSS>6) with or without diabetes |
| **duration** | Duration of hospital stay up to a maximum of 3 months. 1 year total duration. |

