# 2. STUDY OBJECTIVES

**Primary Objective**

Establish the impact of glycaemic variability on outcomes in acute stroke in people with and without diabetes.

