**Stroke Primary outcomes:**

Modified Rankin Scale (MRS) at 90 days

National Institutes of Health Stroke Scale (NIHSS) at 24, 48 and 72 hours

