## 6.3 Telephone follow up at 3 months

Participants who are discharged from the hospital within 3 months will be followed up by the research team via a telephone call (in order to obtain MRS scores).

Participants will be given the option to provide consent to be contacted again for future research.

End of study will be defined as Last Subject Last Visit (LSLV)

7. STATISTICs and data analysis

This is a hypothesis generating study and, as such, we are not proposing a fully-powered study. The data gathered from the proposed work will serve as robust pilot data to support a larger randomised study. At the end of the study, participants with impaired glucose tolerance or diabetes will be sub analysed.

Parametric data will be compared using an independent t-test. Non-parametric data between groups will be compared using a Mann-Whitney test.

Data and all appropriate documentation will be stored for a minimum of 10 years after the completion of the study, including the follow-up period.

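### The two-group tests named in section 7, read against the cohorts the protocol recruits, do not relate glycaemic variability to stroke outcome as the primary objective requires

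*Protocol*

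**What the plan says.** The Primary Objective in section 2 is to "Establish the impact of glycaemic variability on outcomes in acute stroke in people with and without diabetes". The glycaemic primary outcome, which acts as the exposure, is given in the Study Summary as "Mean absolute glucose (MAG) change during initial 72 hours after confirmed stroke". The stroke primary outcomes in section 2 are "Modified Rankin Scale (MRS) at 90 days" and "National Institutes of Health Stroke Scale (NIHSS) at 24, 48 and 72 hours".

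The population is "N=200 with or without diabetes in 1:1 ratio". Sections 3 and 6.2 repeat this as 100 people with and 100 without diabetes.

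Section 7 gives the analysis: "Parametric data will be compared using an independent t-test. Non-parametric data between groups will be compared using a Mann-Whitney test". It does not say which groups are meant. It also announces a sub-analysis of participants with impaired glucose tolerance or diabetes, without a method. It describes the study as hypothesis generating, not fully powered, and as pilot work for a larger randomised study.

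**The concern.** The objective asks how one measured quantity, MAG, relates to others, MRS and NIHSS. The tests named in section 7 compare a single variable between two groups, and the two groups the protocol recruits are defined by diabetes. One such test shows whether MAG differs by diabetes; another shows whether outcome differs by diabetes. Neither puts MAG and outcome into the same analysis.

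Two diabetes contrasts would not provide the size of the MAG-outcome association, overall or within either cohort. Section 1.2 rests on that association in people with diabetes, and the randomised trial planned in section 1.3 would aim to improve outcome by reducing variability.

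**Working it through.** **Inputs from the protocol.** Two cohorts of 100; continuous MAG over 72 hours; ordinal MRS at 90 days; NIHSS at three times; an independent t-test and a Mann-Whitney test. The protocol gives no alpha, effect size or SD, so there is no planned figure to reproduce.

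**Assumptions.** Two-sided alpha of 0.05 and all effect sizes below.

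**Model.** With D = 1 for diabetes and 0 otherwise, and independent standard normal errors:
- MAG = a·D + e1
- Outcome = b·MAG + g·D + e2

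Here b is the association that the objective asks about. The adjusted analysis is a linear model of outcome on MAG and D.

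**Step 1: groups read as diabetes and no diabetes.** Share of 3,000 simulated studies with p < 0.05:

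| Setting | a | b | g | t-test, MAG by diabetes | Mann-Whitney, outcome by diabetes | MAG term adjusted for diabetes |
|---|---|---|---|---|---|---|
| A: no MAG effect | 0.8 | 0 | 0.8 | 100% | about 100% | 4.9% |
| B: MAG effect, no diabetes effect | 0 | 0.3 | 0 | 4.8% | 5.4% | 98% |
| C: MAG effect offset by diabetes | 0.8 | 0.3 | −0.24 | 100% | 4.8% | 99% |

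In C the direct diabetes effect cancels the route through MAG: 0.3 × 0.8 − 0.24 = 0. Both contrasts are positive in A, where MAG does nothing. In B and C, where MAG matters, the outcome contrast stays at about its nominal level. The pair of contrasts does not track b.

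**Step 2: groups read as good and poor outcome, or as high and low MAG.** The same tests then compare MAG between outcome groups, or outcome between MAG groups, without diabetes in the analysis. In setting B this detects the effect in about 90% of studies. With b = 0 and a = 0.8 it is falsely significant as follows:

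| Assumed diabetes-outcome shift g | Unadjusted two-group test | MAG term adjusted for diabetes |
|---|---|---|
| 0.2 SD | about 7% | about 5% |
| 0.4 SD | about 13% | about 5% |
| 0.8 SD | 34% to 38% across simulation runs | about 5% |

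A rerun gave similar rates whether the outcome or MAG was split.

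**Step 3: what the data could support.** The smallest correlation detectable with 80% power is r = tanh[(1.960 + 0.842)/√(n − 3)].
- n = 200: tanh(2.802/14.04) = 0.20
- n = 100, one cohort: tanh(2.802/9.85) = 0.28

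A moderate association is therefore within reach of the planned sample. The shortfall lies in the stated analysis.

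**The case against.** The case for the protocol has four parts.

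- **The groups are not named.** Reading them as diabetes and no diabetes is an inference. The background cites work that compared quartiles or quintiles of variability. A Mann-Whitney test of MRS between high and low MAG would keep the full ordinal scale and relate variability to outcome. This stands in part: that reading gives a link, but a crude one confounded by diabetes, as step 2 shows. The protocol gives no MAG or outcome cut-off that would establish it.
- **A sub-analysis is also planned.** True, so the two tests are not the whole plan. It has no stated method and does not supply the missing link.
- **A statistical analysis plan may exist.** Covariate lists and model details may properly be left to it, and their absence is no fault here. But section 7 does name methods, and those methods do not fit the objective.
- **The study is hypothesis generating.** Section 7 uses this to explain the lack of full power. It does not explain a mismatch between objective and method.

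Two stronger readings are tempting. A reader might infer that the study is unable to answer its objective. The documents do not support that, since MAG, MRS, NIHSS and diabetes status are all to be collected. A reader might also take joint significance of the two diabetes contrasts in setting A as a false-positive rate. It is not: diabetes truly shifts both variables there, and each test correctly rejects its own null hypothesis. The outcome contrast rejects in about 28%, 77% and 100% of studies at assumed shifts of 0.2, 0.4 and 0.8 SD, which is simply its power. The error would come in reading the pair as evidence about MAG.

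**Conclusion.** The point holds in limited form. Under the natural reading of section 7, the analysis as written does not address the primary objective, although the data would allow it. Under the alternative readings it addresses the objective crudely, with false-positive rates from about 7% to between 34% and 38% over the range examined, against about 5% after adjustment for diabetes.

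The mismatch itself follows from the text and needs no simulation. The percentages rest on assumed effect sizes, normal errors, a two-sided 0.05 level and diabetes as the sole simulated confounder. For that last reason, the 5% does not promise that adjustment for diabetes alone would suffice in real data.

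**What to change.** For the primary objective, replace the two test sentences in section 7 with a regression of each stroke primary outcome on continuous 72-hour MAG:

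- **90-day MRS:** for example, ordinal regression with death scored 6.
- **NIHSS at 24, 48 and 72 hours:** for example, a repeated-measures model. State how the overlap in time is handled, because 72-hour MAG includes glucose recorded after the 24- and 48-hour assessments. One option is to use MAG up to each assessment.
- **Covariates in both:** diabetes status, baseline NIHSS and age. Section 4 already requires an NIHSS score and an age check at entry.
- **Reporting:** the MAG effect with a 95% CI overall and within each cohort, with the MAG-by-diabetes interaction labelled exploratory.

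Keep the t-test and Mann-Whitney test for describing the two cohorts, and name those groups. Reword the objective so that it estimates an association instead of establishing an impact, since the design is observational.

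The cost is wording in the protocol or analysis plan, slightly more analysis work and a more modest objective. No further patients or measurements are needed.

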In vitro data has suggested that GV is more deleterious than consistent hyperglycaemia. Human umbilical vein endothelial cells exposed to a glucose concentration alternating between 5 and 20mmol/L every 24 hours show significantly more apoptosis than cells exposed to a constant concentration of 5mmol/L or 20mmol/L over 14 days (Risso A, et al. 2001). Using the same constant and alternating glucose concentrations in human umbilical vein endothelial cells overproduction of reactive oxygen species is highest with oscillating glucose concentrations (Quagliaro L, et al. 2003). In the same sequence of studies expression of the cytokine IL-6 was highest with oscillating glucose concentrations (Piconi L, et al. 2004).

In human proximal tubular cells exposed to increased glucose concentrations (25mmol/L), cell growth, collagen synthesis and cytokine production are elevated, and this is increased further by oscillating the glucose concentration between 25mmol/L and 6.1mmol/L (Jones SC, et al. 1999).

In the critical care scenario, where glucose control is considered important, even in people without diabetes, variability is associated with mortality. In 7049 critically ill subjects the SD of blood glucose concentrations was a significant independent predictor of mortality in the intensive care unit and in hospital (Egi M, et al. 2006). These data have been confirmed by other authors in 3250 subjects with a five-fold mortality increase between the lowest and highest quartiles of standard deviation (Calles-Escandon J, et al. 2010) and in 5728 patients in a study which demonstrated that high variability accompanied by a high mean glucose conferred the highest mortality (Hermanides J, et al. 2010). These data have also been shown in a paediatric intensive care unit where a retrospective review of 1094 patients showed that those in the highest quintile of glycaemic variability had a longer length of stay and significantly elevated mortality (Wintergerst KA, et al. 2006).

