**Glycaemic Secondary outcomes:**

Number hypoglycaemic excursions,

Time (minutes and %) spent in hypoglycaemia (<3.9mmol/L, 70mg/dL)

Time spent in hypoglycaemia (<2.8mmol/L, 50mg/dL)

Time spent in hypoglycaemia (<3.3mmol/L, 60mg/dL)

Time in euglycaemia (3.9-7.8mmol/L, 70-140mg/dL)

Time spent in target (3.9-10mmol/L, 70-180mg/dL)

Time spent in hyperglycaemia (>10mmol/L, 180mg/dL)

Severe hypoglycaemia (3rd party assistance required)

MAD%,

MARD%

Glucose variability, measured by Mean absolute glucose (MAG) and Low blood glucose index (LBGI)

HbA1c and other markers of metabolism

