## 3. STUDY DESIGN

This will be an observational cohort study.

100 consecutive volunteers with an acute stroke (NIHSS score >6) and a previous diagnosis of diabetes who are admitted to Charing Cross Hospital Hospital and 100 people with an acute stroke (NIHSS score >6) without diabetes will be recruited in a 1:1 ratio.

Each participant will remain in the study for the duration of their stay in hospital, up to a maximum of 3 months. 1 year total duration for active recruitment and study conduct.

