# 4. Participant Entry

## 4.1 Pre-registration evaluations

NIHSS Score (this should be greater than 6). Participants will have been admitted to hospital for an acute stroke.

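### The only tests named for the primary objective are unadjusted two-sample tests with undefined groups; they cannot show how glycaemic variability relates to stroke outcome in an observational cohort

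*Protocol*

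**What the plan says.** The Primary Objective is: "Establish the impact of glycaemic variability on outcomes in acute stroke in people with and without diabetes". Section 3 adds: "This will be an observational cohort study". The Study Summary gives the glycaemic primary outcome as "Mean absolute glucose (MAG) change during initial 72 hours after confirmed stroke". The stroke primary outcomes in Section 2 are "Modified Rankin Scale (MRS) at 90 days" and NIHSS at 24, 48 and 72 hours.

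Section 7 (Statistics and data analysis) says: "Parametric data will be compared using an independent t-test". It assigns non-parametric data between groups to a Mann-Whitney test and plans a sub-analysis of participants with impaired glucose tolerance or diabetes. It names no other analysis. The protocol mentions no regression model, covariate, matching or stratified analysis, and does not say which groups the two tests compare.

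**The concern.** The objective is an exposure-outcome question. MAG is the exposure, MRS and NIHSS are the outcomes, and nobody is randomised to a level of variability. Two things go wrong if Section 7 is followed as written.

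First, the tests may not address the question. The only groups that the design sets up are people with and without diabetes, recruited 1:1. Comparing MAG between them, and separately MRS between them, does not show whether MAG is associated with MRS.

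Second, if the groups are instead formed from MAG, the comparison is unadjusted. Section 1.1 associates hyperglycaemia with adverse outcome and reports, from critical care, that "high variability accompanied by a high mean glucose conferred the highest mortality". Entry NIHSS has a floor (above 6) and no ceiling, so severity at entry can vary widely. A difference in outcome between high and low MAG could therefore come from glucose level or from severity. What is at stake is the interpretation: Section 1.3 plans a randomised trial with reduced variability as a goal, and Section 7 offers these data as pilot support for a larger randomised study.

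**Working it through.** **Is there a figure to reproduce?** No. The protocol states no alpha, power or effect size, and says that the study is not fully powered.

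**The two readings of the groups**

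| Reading | What the tests compare | Does it relate MAG to outcome? | Adjusted? |
|---|---|---|---|
| Diabetes v no diabetes (the design's groups) | MAG, MRS or NIHSS by diabetes status | No | No |
| High v low MAG (not stated) | MRS or NIHSS by MAG level | Yes | No |

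Adding covariates to the first reading would not cure it; a model with MAG as the exposure is needed.

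**How large could confounding be under the second reading?** From the protocol: N = 200. Assumed: every correlation and path coefficient below, the median split on MAG, and the distribution of the 7-level MRS. The true effect of MAG is set to zero throughout.

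*Step 1, one confounder, correlation scale.* If entry NIHSS is the only link, the induced correlation is r = r(MAG, NIHSS) × r(NIHSS, MRS). With SE = 1/√(200 − 3) = 1/√197 on the Fisher z scale, the probability of p < 0.05 is P(|Z + atanh(r)·√197| > 1.96), where Z is standard normal.

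| Assumed correlations | Induced r | atanh(r)·√197 | P(p < 0.05) |
|---|---|---|---|
| 0.2 × 0.4 | 0.08 | 1.125 | 20% |
| 0.3 × 0.5 | 0.15 | 2.121 | 56% |
| 0.4 × 0.5 | 0.20 | 2.845 | 81% |

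These are rates for a test of correlation, which the protocol does not name. With a t-test on a median split of MAG, simulation of the same three cases gives about 15%, 39% and 62%.

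*Step 2, two confounders, the named tests.* Simulation of 2,000 studies of 200 per scenario. High and low MAG (median split) were compared on a 7-level MRS. The adjusted comparator was a linear model of MRS on continuous MAG, severity and mean glucose. Coefficients are in the order severity→MAG, glucose→MAG, severity→MRS, glucose→MRS.

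| Assumed coefficients | Mann-Whitney, p < 0.05 | Spurious MRS difference | Adjusted model, p < 0.05 |
|---|---|---|---|
| 0, 0, 0.5, 0.2 | 4.2% | 0.00 | 5.0% |
| 0.1, 0.3, 0.5, 0.2 | 22.6% | 0.32 | 5.5% |
| 0.2, 0.3, 0.5, 0.2 | 40.8% | 0.46 | 4.3% |
| 0.2, 0.5, 0.5, 0.2 | 58.6% | 0.58 | 5.4% |
| 0.3, 0.5, 0.5, 0.3 | 90.4% | 0.85 | 5.0% |

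The t-test rates are within 1 percentage point of the Mann-Whitney rates. The first row is the control: if neither factor is related to MAG, the unadjusted test keeps its 5% level. The adjusted model does well partly because both confounders are measured without error here, which real data will not match.

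**The case against.** **A SAP may add models.** Covariate lists are commonly left to a SAP, and Section 7 does not say that its tests are the only analyses. This stands as a limit: the point concerns the analyses that the protocol names. It does not remove the point, because the protocol has chosen tests, and those tests cannot answer the stated objective.

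**The confounding links are not all in the documents.** A reader might infer that severe strokes raise MAG, or that MAG rises with mean glucose, so that the unadjusted result is bound to be false. The protocol supports neither statement. No section links entry NIHSS to MAG. MAG measures change, and a flat trace at any level gives zero. The critical-care report describes a joint association with mortality; it does not show that mean glucose confounds variability. What remains is that both factors are plausible alternative explanations, which the named tests cannot rule out.

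**Some control exists by design.** People over 80 or with premorbid MRS above 2 are excluded, time above 10 mmol/L and HbA1c are recorded, and a diabetes sub-analysis is planned. This narrows age and prior disability and captures the burden of hyperglycaemia. It adjusts for neither entry severity nor glucose level.

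**The study is hypothesis generating, and the next trial would randomise.** This stands against any claim that a false signal passes straight into that trial: it is already planned, and the protocol does not make it conditional on a significant result here. But the label excuses low power, not confounding. A larger sample would make a confounded difference more significant, not less.

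**Other variability measures.** One could ask for SD, coefficient of variation or a different place for LBGI. That is preference, and Section 1.1 gives its own reason for caution about SD.

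**Conclusion.** The point holds for what the protocol names. Followed as written, Section 7 gives either no MAG-outcome analysis or an unadjusted one, and neither supports a statement about the impact of variability in an observational cohort. This conclusion needs no assumed number.

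The size of any bias is unknown. The range of 23% to 90% false positives applies only if MAG is split at its median and the assumed links to severity and mean glucose hold; with no such links to MAG it falls to the nominal level. It should not be read as an estimate for this study.

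**What to change.** Replace the two-sample tests for the primary objective, in the protocol or the SAP, with the following.

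1. An ordinal model of 90-day MRS on 72-hour MAG as a continuous exposure, adjusted for entry NIHSS, age, premorbid MRS and diabetes status.
2. A model of NIHSS at 24, 48 and 72 hours on MAG, with entry NIHSS as a covariate. The MAG window runs past the first two assessments, so these results need particular care in wording.
3. Each model reported without and with CGM mean glucose over the same window. Any statement about variability itself should rest on the model with it.
4. Results worded as association. If the t-test and Mann-Whitney test are kept for describing diabetes v no diabetes, say so and define the groups.

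No new data are needed. Entry NIHSS, age, premorbid MRS and diabetes status are required for eligibility or cohort assignment (Sections 4.1 to 4.3 and 6.2), and mean glucose comes from the CGM trace that yields MAG. The statistical cost is a wider interval for MAG in the mean-glucose-adjusted model, to the extent that the two are correlated.

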# 8. regulatory issues

## 8.1 Ethics approval

The Study Coordination Centre has obtained approval from the xxx Research Ethics Committee (REC) and Health Regulator Authority (HRA). The study must also receive confirmation of capacity and capability from each participating NHS Trust before accepting participants into the study or any research activity is carried out. The study will be conducted in accordance with the recommendations for physicians involved in research on human subjects adopted by the 18th World Medical Assembly, Helsinki 1964 and later revisions.

## 8.2 Consent

Consent to enter the study must be sought from each participant only after a full explanation has been given, an information leaflet offered and time allowed for consideration. Signed participant consent should be obtained. The right of the participant to refuse to participate without giving reasons must be respected. After the participant has entered the study the clinician remains free to give alternative treatment to that specified in the protocol at any stage if he/she feels it is in the participant’s best interest, but the reasons for doing so should be recorded. In these cases the participants remain within the study for the purposes of follow-up and data analysis. All participants are free to withdraw at any time from the protocol treatment without giving reasons and without prejudicing further treatment. Refer to section on recruitment and consent for further details.

## 8.3 Confidentiality

The Chief Investigator will preserve the confidentiality of participants taking part in the study and is registered under the Data Protection Act. Confidentiality of data will be preserved during data transmission via the use of anonymised codes. Participants will be assigned codes based on order of enrolment and site at which they are enrolled (G-VAS-001 etc.). Identifiable personal information will be stored securely in a locked room at Imperial College Healthcare NHS Trust and Imperial College London. Pseudonymised data will be stored on Imperial College Healthcare NHS Trust computers, Imperial college London computers or encrypted laptop computers (either ICL/ICHT). Data will be accessible only to the Research Team and for audit. Pseudonymised data will be used for analysis. The data will be stored at Imperial College London for 10 years. The data custodian is [name].

